### Randomisation

The researcher will complete a checklist, confirming eligibility, obtain written (or verbal audiorecorded consent from the subject due to current pandemic COVID-19 SOPs), and complete the baseline measures. The researcher will contact the randomisation centre, who will recheck eligibility, record baseline measures and assign a participant trial number. Treatment assignment will then be determined using stochastic minimisation controlling for gender, age and type of self-harm behaviour. The independent statistician would inform the project manager of the random assignments, but this information would not be shared with research staff, so that they remain unaware of whether a particular participant receives YCMAP or not. Participants assigned to the YCMAP would then be contacted by a therapist, who will arrange an initial meeting within 2–4 weeks after baseline to start the intervention. Participants in the TAU group would be informed of their allocation to this group after randomisation has taken place.

### Recruitment and baseline assessment

Potentially eligible individuals will be identified by clinical staff at the participating recruitment sites. An age appropriate version of the participant information sheet (PIS) will be provided alongside the standard PIS, so both the parent/guardian and child can access this information. For individuals who cannot read, information about the study will be summarised by the clinician for them. Consent will be obtained from the parent/guardian along with consent from the participating young person (The Nuffield Council for Bioethics guidance suggests that consent rather than assent should be sought from young people in research). Therefore, it is ensured and clearly mentioned in the PIS for both the young people and their parents that it is mandatory for parents/guardians to consent for young person to participate in the study.

### Intervention

YCMAP is a ‘Youth culturally adapted manual assisted psychological intervention’ based on CBT principles. It comprises of 8–10 sessions delivered over 3 months. The first eight sessions are offered weekly and further sessions fortnightly on a one to one basis and each session lasts for about 60 min. The YCMAP has been culturally adapted with permission from ‘CMAP’,^15^ ‘Life after self-harm’^27^ and ‘Cutting down: A CBT workbook for treating young people who self-harm’.^28^ The intervention includes psycho-education and a comprehensive cognitive behavioural assessment of the self-harm attempt using virtual stories of four young people. The therapy focuses on current problems that contributed to the self-harm episode. Therapists and adolescent clients choose from a list of techniques those which are most relevant to the client’s problems. Therapy is therefore adapted to fit with the clients problems and primarily utilises problem solving, CBT and dialectical therapy strategies to bring about change.

To help determine the most appropriate coping strategy a coping tree is designed. Training in assertiveness and anger management are offered to help the young person to develop resilience to cope with stress. To the existing YCMAP we will also aim to review the look and feel of the resource by including licensed content from My Big Life—a course developed by our collaborative partner Five Areas Limited. This accessible, story-based approach uses illustrations of young people facing different scenarios at home and at school to illustrate key CBT-based concepts: Understanding your feelings-How to get a Big Life (behavioural activation)—Thinking in a Big Life way (identifying and changing thoughts that upset and affect how you feel)—Relaxation approaches—Building inner confidence—Practice scenarios—Trainer notes and linked worksheets/prompt cards and posters. Asian versions of the course already exist with amended artwork. As part of the development programme selected content will be added to the course and trainer notes will be modified (based on feedback) as needed.

All research staff will be required to have at least an undergraduate level degree in a relevant area (eg, psychology) and will be trained in ‘Good Clinical Practice’ in research, consent process and use of the assessment measures. Regular supervision meetings will be arranged for research staff and therapists for case discussions, identifying and managing distress in participants. A study protocol will be in place prior to the start of the trial. This will include details about how to manage difficult situations arising in research, safety and lone working arrangements.

### Treatment as usual

Local psychiatric, medical and primary care services provide standard routine care according to their clinical judgement and available resources. We will administer Client Services Receipt Interview (CSRI)^29^ to obtain details regarding treatment received by each study participant. These participants will receive an initial assessment along with TAU as ascertained by their treating doctor at the hospital or their general practitioner (GP). The current practice is that self-harm patients are not routinely referred to mental health services. Research staff will record the nature and intensity of the routine care delivered for each participant.

### PPIE group

This group will help to ensure that the research agenda for self-harm and suicide prevention studies is informed by and aligned with service users and carer priorities.

### Statistical analysis

Statistical analysis will be based on intention-to-treat principles, subject to the availability of data. During the course of the trial, periodic random quality checks of data will be carried out by the trial statistician blind to treatment allocation. Once data entry has been completed, preliminary data analysis will be carried out blind to treatment allocation, prior to unblinding. The results of the trial will follow the standard Consolidated Standards of Reporting Trials recommendations. Baseline and follow-up data will be summarised using the appropriate descriptive statistics and graphical summaries. Treatment effects will be presented with 95% CIs. We will investigate baseline factors that predict nonresponse using a logistic random effects model as non-response may be clustered by therapy group. The statistical analysis of the primary outcome measure (repetition of the self-harm episode within 12 months) will be based on a logistic random effects model with randomised treatment, age, gender and type of self-harm as fixed effects and a random effect of therapist in the treatment arm, with individuals in the control arm being treated as clusters of size 1. The continuous secondary outcome measures will calculate treatment effects using a linear mixed model, with a random effect of therapist and the set of baseline covariates as above including baseline values of the outcome where available. A single model will be fitted across all time points, with a fixed effect for time, and interactions between time and treatment group. There will be no adjustment to secondary outcomes CIs for multiple testing. Binary secondary outcomes will take a similar approach to continuous outcomes, but will use logistic random effects models.

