## Introduction

Suicide is one of the major public health concerns globally with 700 000 suicides each year across the globe.^1^ More than 77% of suicides occur in low-income and middle-income countries (LMICs). However, there are now major concerns about increasing rates of self-harm and suicide among young people in high-income countries such as USA^2^ and Europe.^3^ Overall, suicide is the second-leading cause of death in individuals between 15 and 29 years old.^1^ A recent review reported suicide rates in South Asia to be higher than the global average.^4^ However, such figures are likely to be an underestimate due to a lack of accurate data on suicide in Pakistan^5^ and in many other LMICs.^6^

In Pakistan, a conservative Islamic state, policies are changing but suicide and self-harm (defined below) remain criminal acts and are condemned both socially and religiously as a moral wrong. Suicide and self-harm are often considered taboo subjects across the country, thus contributing to a lack of evidence and under-reporting.^4^ There is, however, accumulating evidence that both self-harm and suicide rates have been increasing in Pakistan but there continues to be notable gaps in evidence.^4^ In a systematic review of mental health studies of adolescents in India, it was found that self-harm is particularly problematic in young people, with 3 months prevalence ranging from 3.9% to 25.4% in community-based studies.^7 8^ Self-harm is one of the strongest predictors of death by suicide.^9^ Self-harm also carries a substantial economic impact and has been associated with large treatment costs in Pakistan.^10^ Adolescents with a history of self-harm are at a higher risk of repeating this later in life,^11^ thus there is an important need to develop effective interventions in order to avoid long-term burden.

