### Sample size

The sample size is based on the primary outcome, repetition of self-harm in a 12-month period (yes/no). The TAU arm of the study has an expected self-harm rate of 20%.^7^ A clinically important effect would be a reduction to 7.5% in the intervention group. Under these presumptions, and assuming a 5% significance level and 90% power, a study with no clustering would require 158 patients per arm. The study has a partially nested design due to therapist clustering in the YCMAP arm. Our sample size calculation has taken account of this by adjusting the sample size upwards, conservatively assuming clustering in both arms. Based on previous analysis of therapist trials, we believe that the intraclass correlation coefficient (ICC) is likely to have a value between 0.01 and 0.05 for this type of outcome measure. Assuming an ICC of 0.05, and a cluster size of 16 patients per therapist, a design effect of 1.75 is calculated. This increases the numbers required to 277 per arm. Furthermore, based on our previous work there is expected to be a 15% loss to follow-up, and so the final numbers recruited will be 326 per arm, with a total sample of 652 participants.

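### The primary model adjusts only for the minimisation factors and leaves out the baseline severity scores that the trial already collects; one or two should be named before unblinding

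*Protocol article*

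**What the plan says.** **Primary model.** The protocol article, Statistical analysis, specifies a logistic random effects model for repetition within 12 months. The fixed effects are randomised treatment, age, gender and type of self-harm, with a therapist random effect in the YCMAP arm. The Randomisation section names gender, age and type of self-harm as the minimisation factors, so the covariate list is exactly that set.

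**Secondary models.** The continuous secondary outcomes use the same covariates, "including baseline values of the outcome where available".

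**Baseline data.** The Objectives section lists scales for suicidal ideation, hopelessness and distress and schedules assessments from baseline onwards. The Introduction names hopelessness among the common risk factors for self-harm. It also states: "Adolescents with a history of self-harm are at a higher risk of repeating this later in life".

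**Loss to follow-up.** The Sample size section allows for 15% loss. The Statistical analysis section states: "Statistical analysis will be based on intention-to-treat principles, subject to the availability of data". It then adds: "We will investigate baseline factors that predict nonresponse using a logistic random effects model as non-response may be clustered by therapy group".

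**The concern.** The primary outcome carries the trial's main conclusion, yet its model uses less baseline information than the continuous secondary models do. Scores for ideation, hopelessness and distress will be on file before randomisation, and the article itself treats hopelessness as a risk factor.

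Two things are at stake. The first is power: in a logistic model, conditioning on a prognostic covariate moves the treatment odds ratio further from 1, and this can outweigh the accompanying rise in its standard error. The second is loss to follow-up. If more severely affected adolescents drop out at a different rate in one arm than in the other, an available-case odds ratio without severity in the model is biased. The bias can run towards a false benefit, and a larger sample does not remove it.

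**Working it through.** **1. The plan's own sample size.** Inputs from the Sample size section: 20% under TAU, and "A clinically important effect would be a reduction to 7.5% in the intervention group". The unclustered requirement is stated as "assuming a 5% significance level and 90% power, a study with no clustering would require 158 patients per arm". Pooled-variance formula, two-sided 5%:

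- mean rate = (0.20 + 0.075)/2 = 0.1375
- n = [1.960 × √(2 × 0.1375 × 0.8625) + 1.2816 × √(0.20 × 0.80 + 0.075 × 0.925)]² / 0.125²
- = (0.9545 + 0.6138)² / 0.015625 = 157.4, so 158 per arm
- design effect = 1 + 15 × 0.05 = 1.75; 158 × 1.75 = 276.5, so 277
- 277/0.85 = 325.9, so 326 per arm and 652 in total

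The chain reproduces exactly, including the allowance for loss.

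**2. Events available.** 277 × 0.20 + 277 × 0.075 = 55.4 + 20.8, about 76.

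**3. Power with and without a severity covariate.** The documents give no prognostic strength, so a range is assumed. The simulation used 158 per arm (the size net of clustering), the plan's rates and 4,000 trials per row.

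| Assumed OR per SD of severity | Without | With | Gain (points) |
|---|---|---|---|
| 1.3 | 90.3% | 90.4% | 0.1 |
| 1.5 | 90.7% | 91.3% | 0.6 |
| 2.0 | 90.4% | 91.7% | 1.3 |
| 2.5 | 90.6% | 92.5% | 1.9 |

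The Monte Carlo standard error is about 0.5 points per figure, so the gain is about 0 to 2 points.

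**4. Loss that depends on severity, at the plan's effect.** The true log odds ratio is ln[(0.075/0.925)/(0.20/0.80)] = −1.126. Assumptions: 15% loss per arm, severity OR 1.5 to 2.0 per SD for repetition, and a log odds of loss of 0.7 per SD where dependence is present. Available-case analysis without severity gives:

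- same dependence in both arms: −1.129 to −1.130, essentially no bias
- dependence in one arm only: −1.05 to −1.20, a shift of about 0.04 to 0.08
- opposite dependence in the two arms: −1.00 to −1.27, a shift of about 0.08 to 0.13

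**5. The same question under a true null.** With 20% repetition in both arms, 15% loss per arm, loss tied to severity in the YCMAP arm only (OR 2 to 3 per SD) and severity tied to repetition (OR 1.5 to 2 per SD), the odds ratio without severity is about 0.90 to 0.96. In logs, ln 0.899 = −0.106 and ln 0.964 = −0.037, which is about 0.04 to 0.11. On the risk scale, 0.25 × 0.964 = 0.241 gives a risk of 19.4%, and 0.25 × 0.899 = 0.225 gives 18.4%. That is 0.6 to 1.6 points of false benefit. With severity in the model the odds ratio returns to about 1.00.

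**6. Scale.** At the effective 158 per arm with 20% in both arms, the standard error of the log odds ratio is √[2/(158 × 0.20 × 0.80)] = 0.28. A bias of 0.04 to 0.11 is therefore about 0.1 to 0.4 of a standard error. The planned difference is 12.5 points.

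**The case against.** The strongest reply is that adjusting a binary outcome for the minimisation factors alone is accepted practice, is fixed in advance, and contains no error. That stands. The existing covariates should remain, and what is missing is an inexpensive improvement.

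The contrast with the secondary models is also weaker than it looks. Those models use the baseline value of the same outcome. Here every participant has self-harmed within three months of identification, so the baseline value of the yes/no outcome is the same for all and cannot be a covariate. For the same reason, the Introduction's statement about a history of self-harm does not separate one participant from another. Only graded measures could: a scale score or a number of prior episodes. The article does not say that the adapted interview yields such a number at baseline.

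A reader might go further and infer that the 15% loss is left uncorrected, that the non-response model leads nowhere, or that the analysis is valid only if loss depends on nothing but the minimisation factors. The documents do not support this:

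- The numbers lost are already in the sample size (277/0.85 = 326).
- Imputation and sensitivity analyses are commonly left to the analysis plan, which is not at hand. Restricting the analysis to available data does not rule them out.
- Loss tied to severity equally in both arms barely moves the odds ratio (step 4). Bias needs arm-specific dependence. The article mentions that non-response may cluster by therapy group, which makes a difference between arms conceivable but does not show one.

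Nor is a material loss of precision shown. The gain forgone is at most about 2 points of power, and it does not come from a smaller standard error.

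**Conclusion.** The point holds in a limited form. As stated, the primary model conditions on the minimisation factors and omits baseline severity scores that are collected and likely to be prognostic. Naming one or two of them would add about 0 to 2 points of power. It would also remove a bias of about 0.04 to 0.11 on the log odds ratio if loss depends on severity in one arm only; if the dependence runs in opposite directions in the two arms, the bias is up to about 0.13. The protection covers only loss explained by the covariates that are included.

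All the associations are assumed, because the documents give neither prognostic strengths nor patterns of loss. The power and effect-size calculations handle clustering through the effective sample size and do not fit the therapist effect. The stated sample size is unaffected. This is a worthwhile, low-cost improvement to the primary model, and it is not evidence that the planned analysis is invalid or that missing data go unhandled.

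**What to change.** Before unblinding, state in the analysis plan that the primary model includes, besides age, gender and type of self-harm, one or two named baseline severity covariates. The Beck suicidal ideation score is the natural choice. The number of prior self-harm episodes can be the second, if the baseline interview records it.

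Do not add covariates to the primary model because the non-response analysis selects them. That would make the confirmatory model depend on the data. If the selection is made blind to allocation, it also cannot reveal dependence that differs by arm, which is the case that matters. Any such predictors belong in a sensitivity or imputation analysis, and the plan should say so in a sentence.

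Cost: a few lines of text and no new data collection if the scores are recorded as scheduled. The model gains one or two parameters against about 76 expected events. The conditional odds ratio will differ slightly from the one without severity, so a standardised risk difference can be reported beside it.

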### Design

A multicentre rater blind randomised controlled trial (RCT) with randomisation by individual participants in order to compare the YCMAP in addition to TAU with TAU alone.

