### Study site and population

Study sites are all participating primary care clinics, emergency departments and medical wards of general hospitals in five major cities of Pakistan, Karachi, Hyderabad, Lahore, Multan and Rawalpindi.

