### Economic evaluation

The economic evaluation will take a societal perspective that incorporates the costs of both formal and informal healthcare and other relevant economic impacts such as on education. It will include financial impacts on providers and out of pocket payments by participants and their families. The use and payment for services will be collected using the CSRI^29^ with patients and their families at baseline and at each follow-up assessment. The use of the YCMAP intervention will be recorded separately by the trial team. Appropriate unit costs will be collected and attached to individual-level resource use quantities to estimate total care costs for each individual. Cost estimates for the YCMAP intervention will include (1) the salary of the therapists and (2) indirect costs like session preparation, supervision, on-costs and capital overheads. Comparisons of total costs between the YCMAP and TAU arms will be based on non-parametric bootstrapped regressions (with covariates for baseline costs, outcome measures and other key baseline factors) to account for the likely non-normal distribution in costs. An inital analysis will examine whether any additional costs associated with the YCMAP intervention are offset by savings elsewhere.

More formal assessments of cost-effectiveness will link between-arm differences in average costs with between-arm differences in (1) the primary outcome measure, repetition of self-harm (SASII) and (2) quality-adjusted life-year (QALY) gains. QALYs will be estimated by applying relevant utility weights to health states measured through EuroQol-5 Dimensions-Youth (EQ-5D-Y).^23 30^ Costs and outcomes will be linked in the form of incremental cost-effectiveness ratios where relevant, and cost-effectiveness acceptability curves based on the net benefit approach. As per the clinical effectiveness analyses, we will use an intention-to-treat approach for all economic analyses.

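### City is in neither the minimisation nor the primary and secondary outcome models of a five-city trial, so city differences can enter the YCMAP therapist variance and widen intervals

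*Protocol article*

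**What the plan says.** The Design section describes "A multicentre rater blind randomised controlled trial (RCT) with randomisation by individual participants". Study site and population places the sites in "five major cities of Pakistan, Karachi, Hyderabad, Lahore, Multan and Rawalpindi". Under Treatment as usual, routine care is left to local services, so the comparator may differ from place to place.

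Randomisation states: "Treatment assignment will then be determined using stochastic minimisation controlling for gender, age and type of self-harm behaviour".

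Statistical analysis specifies a mixed logistic regression for the primary outcome: "with randomised treatment, age, gender and type of self-harm as fixed effects and a random effect of therapist in the treatment arm". Usual-care participants have no trial therapist, and the plan deals with them thus: "with individuals in the control arm being treated as clusters of size 1". The continuous secondary outcomes use a linear mixed model "with a random effect of therapist and the set of baseline covariates as above", plus the baseline value where available. Binary secondary outcomes are to be handled similarly.

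These lists are written out in full, and none names city, centre or site. Two other models are left open. The cost regressions are specified "with covariates for baseline costs, outcome measures and other key baseline factors", and the covariates of the non-response model are not listed.

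**The concern.** Sessions are one to one and begin with a meeting that the therapist arranges, so a therapist will probably see participants from one city only. In that case therapist and city overlap in the YCMAP arm. With no city term, differences in case mix and local services can only appear as therapist variance. In the usual-care arm the same differences have no term at all.

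Three things are at stake:

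- the width of the confidence intervals;
- the meaning of the therapist ICC;
- the meaning of the primary odds ratio, since YCMAP is conditioned on city through therapist while usual care is averaged over cities.

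Chance imbalance between cities is also left uncorrected, by allocation and by analysis.

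**Working it through.** **1. The plan's own figure.** From Sample size: 20% v 7.5%, 5% significance (taken as two-sided), 90% power. The pooled two-proportion formula gives 157.4, so 158 per arm. The design effect is 1 + (16 − 1) × 0.05 = 1.75, and 158 × 1.75 = 276.5, so 277. Then 277 / 0.85 = 325.9, so 326 per arm and 652 in total. All of this reproduces. Expected events among those analysed are 277 × 0.20 + 277 × 0.075 = 76. The planned odds ratio is (0.075/0.925) / (0.20/0.80) = 0.324, a log-odds ratio of −1.126.

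**2. Assumptions the article does not supply.** Five equal cities; 20 therapists (326 / 16 ≈ 20), four per city; allocation not balanced by city; a city SD on the logit scale of 0.25, 0.5 or 0.75. Around a 20% rate, one SD either way is 16 to 24%, 13 to 29% or 11 to 35%. The therapist ICC is the planned 0.05, an SD of √(0.05/0.95 × π²/3) = 0.42.

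**3. Primary model.** The stated model was simulated with and without city fixed effects on the same data (554 analysed, 1,500 runs per scenario; age, gender and type of self-harm omitted). At the planned effect, without v with city:

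| City SD | Estimated therapist SD | Mean SE of log-odds ratio | SE ratio | Median log-odds ratio | Power |
|---|---|---|---|---|---|
| 0 | 0.31 v 0.25 | 0.321 v 0.315 | 1.02 | −1.140 v −1.131 | 98.1 v 97.8% |
| 0.25 | 0.35 v 0.25 | 0.329 v 0.317 | 1.04 | −1.153 v −1.131 | 97.9 v 97.7% |
| 0.5 | 0.47 v 0.26 | 0.353 v 0.323 | 1.09 | −1.190 v −1.141 | 97.5 v 97.2% |
| 0.75 | 0.64 v 0.25 | 0.392 v 0.328 | 1.20 | −1.237 v −1.143 | 96.1 v 96.3% |

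The therapist SD without city doubles as city variation grows; with city it stays at about 0.25. At city SD 0.75 the median odds ratio is 0.29 without city and 0.32 with it.

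With no treatment effect, the median log-odds ratio without city is −0.015 / −0.063 / −0.121 at city SD 0.25 / 0.5 / 0.75 (odds ratios 0.99 / 0.94 / 0.89). With city it is about 0. Rejection is 3.4 to 4.3% without city and 5.9 to 6.6% with it.

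For a smaller effect (20% v 11%), power over the four city SDs is 75.3 / 76.1 / 73.5 / 73.0% without city and 75.7 / 75.7 / 72.5 / 71.7% with it. Simulation error is about 1.1 points there and 0.4 near 98%.

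**4. Continuous secondary outcomes.** Normal theory at one time point, total variance 1, n = 277 per arm, k = 20 therapists, therapist share t = 0.05, city share c, residual e = 1 − c − t.

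- Model SE without city: √[(t + c)/k + e/n + 1/n]
- SE with city: √[t/k + e/n + (e + t)/n]
- True SD of the estimate without city: √[(SE with city)² + 2c/n]. City effects are common to both arms, so only chance imbalance contributes.
- Reference difference: d = (1.960 + 1.282) × √(2 × 1.75/277) = 0.364 SD
- Power without city: Φ[(d − 1.96 × model SE) / true SD]

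| City share | Model SE without v with city | Ratio | True SD without city | Rejection under the null | Power without v with city | Loss (points) |
|---|---|---|---|---|---|---|
| 1% | 0.1000 v 0.0973 | 1.03 | 0.0977 | 4.5% | 95.8 v 96.3% | 0.5 |
| 2% | 0.1023 v 0.0969 | 1.06 | 0.0977 | 4.0% | 95.3 v 96.4% | 1.1 |
| 5% | 0.1089 v 0.0958 | 1.14 | 0.0977 | 2.9% | 93.9 v 96.7% | 2.9 |
| 10% | 0.1191 v 0.0939 | 1.27 | 0.0977 | 1.7% | 91.0 v 97.3% | 6.3 |

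Using the model SE as if it were the true SD would put the losses at about 1 to 11 points. That overstates them, because the model SE exceeds the real sampling variation.

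**The case against.** The strongest reply is that randomisation is individual and not stratified by city, so leaving out a prognostic covariate does not invalidate the comparison. The primary test keeps its error rate, and power at the planned effect stays above 96% either way, helped by applying the design effect to both arms. This stands. A reader might infer from the wider SE that the primary outcome loses power. It does not, because the estimate moves away from zero along with the SE.

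Two other stronger readings also fail. One is that no analysis model allows for city: the cost and non-response covariates are open and do not exclude it. The other is that the therapist variance is contaminated in both arms: usual-care participants are clusters of size 1, so absorption occurs only under YCMAP.

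Therapists working within one city is an inference. The article does not state it or say that therapy is face to face, and the COVID-19 changes are in a supplement not shown. Delivery across cities would weaken the absorption.

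The proposed remedy has a cost too: some runs gave null rejection slightly above 5%. What the reply does not remove is the wider intervals, the mislabelled ICC and the shifted odds ratio.

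**Conclusion.** The point holds as one of precision and interpretation, worth correcting because the change is cheap. The minimisation factors and the primary and secondary outcome models are stated without city. If therapists are nested in city, the reported therapist ICC mixes therapist and city. The primary SE is then roughly 4 to 20% larger than it need be, and the odds ratio shifts modestly towards apparent YCMAP benefit (away from 1 when the true effect is nil or beneficial). Primary power is essentially unaffected. Continuous secondary outcomes have an SE about 3 to 27% too large, a conservative test and a power loss of roughly 0.5 to 6 points.

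Every size rests on an assumed city variance, since the article gives none. With little variation between cities the effect is negligible.

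**What to change.** Before unblinding, add city as a fixed effect to the primary model and to the continuous and binary secondary outcome models, keeping the therapist random effect in the YCMAP arm. If recruitment is still open, add city as a minimisation factor for the remaining participants. State in the analysis plan whether therapists work in one city only.

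The cost is one covariate, which the recruiting site should already supply, and 4 degrees of freedom against about 76 expected events. Null rejection with city fixed effects ran from about 4 to 6.6% across simulations, so specify a small-sample correction. If the fixed effects prove unstable, the fallback is a random city intercept common to both arms. The cost and non-response models need only a statement that city is among their covariates.
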